#### Cognitive assessments

The assessors conducting cognitive tests will be blinded to the group allocation of the patients. Moreover, the timing of the cognitive assessments will coincide with the time points of clinical evaluations. The WASI will be utilized to evaluate intellectual function. Consisting of four subtests, the WASI assesses two verbal aspects of crystallized intelligence (vocabulary and similarities) and two nonverbal measures of fluid intelligence (block design and matrix reasoning). While the WASI subtests share similarities with those found in the Wechsler Adult Intelligence Scale – Third Edition, they feature distinct items. Cognitive function will be assessed in the study using a battery of eight tests, with the Hopkins Verbal Learning Test-Revised (HVLT-R) designated as the primary cognitive outcome (evaluating verbal learning and memory). The remaining seven tests serve as secondary cognitive outcomes: Trail Making Test Part A (TMT-A), Brief Assessment of Cognition in Schizophrenia, Symbol Coding (BACS SC), Category Fluency Test, Continuous Performance Test-Identical Pairs version (CPT-IP), Wechsler Memory Scale, Third Edition, Spatial Span Test (WMS-III SS), Brief Visuospatial Memory Test, Revised Edition (BVMT-R), and Neuropsychological Assessment Battery: Mazes Test (NAB Mazes). These tests encompass various cognitive domains such as processing speed, attention, verbal and visual learning, reasoning, problem-solving, and working memory. Test-retest reliability in a prior Chinese sample ranged from 0.73 to 0.94 (35).

#### EEG acquisition

Participants will be seated in a dimly lit, sound-attenuated, and electrically shielded room for EEG data collection. EEG data will be recorded using a 64-channel electrode cap (Brain Products Inc., Bavaria, Germany). Electrodes for electrooculography (EOG) will be positioned below the left eye and above the right eyebrow. Bilateral mastoids will be utilized as reference electrodes, with AFz serving as the ground electrode. EEG signals will be digitized at a sampling rate of 1000 Hz and bandpass filtered between 0.016 and 200 Hz using filters from Brain Products Inc. Electrode impedance will be maintained below 5 kΩ throughout EEG data collection. Participants will be instructed to sit comfortably with their eyes closed for 5 minutes and then with their eyes open for another 5 minutes.

Offline preprocessing and subsequent analysis of resting state EEG (rsEEG) data will be conducted using EEGLAB (36) and MATLAB (MathWorks, Natick, Massachusetts). The EEG data preprocessing pipeline will involve several steps to ensure data quality and prepare it for analysis. This included bandpass filtering between 0.5 and 70 Hz with notch filtering at 50 Hz, downsampling to 512 Hz, and visual inspection to remove epochs with severe artifacts. Independent component analysis (ICA) will be used to remove blink and horizontal eye movement artifacts, followed by interpolation of bad channels and re-referencing to the average reference. Subsequently, artifact-free segments of 60 seconds will be selected for power spectral density estimation using Welch’s method with a Hamming window of 2 seconds and 50% overlap between segments, resulting in a frequency resolution of 0.5 Hz (37). Absolute power values will be calculated for predefined frequency bands, including delta (1–4 Hz), theta (4–8 Hz), alpha1 (8–10 Hz), alpha2 (10-12.5 Hz), beta1 (12.5-18.5 Hz), and beta2 (18.5–30 Hz). Additionally, relative power will be computed as the proportion of power within each specific frequency band relative to the total power across all frequency bands. Analyses of EEG data are exploratory and aimed at identifying potential associations with treatment outcomes.

#### ECG acquisition

All participants will undergo 10-minute resting ECG monitoring concurrent with the EEG recording. Participants will be seated comfortably in a quiet room and instructed to maintain even breathing, avoid body movements, and refrain from talking. ECG signals will be recorded using a single-channel system with three electrodes: the red electrode placed on the right forearm, the black electrode on the left forearm, and the yellow electrode on the left shank. Data will be collected using a portable electronic analyzer and computerized analysis system (Heart Rate Analyzer HW6C, Medeia Co., Ltd., Santa Barbara, CA, USA) at a sampling rate of 1000 Hz.

Subsequently, ECG signals will undergo preprocessing to identify artifacts and will be transformed into R-R inter-beat interval (RRI) time series using the NeuroKit2, a standardized neurophysiological signal processing toolbox developed in Python. The toolbox will analyze and extract HRV indices from the RRI series. In this study, utilizing 5-minute ultra-short-term ECG recordings, heart rate and a total of 14 HRV indices will be extracted and included in the analyses:

1. HR (bpm): Mean heart rate times per minute

Time-domain HRV Indices

2. SDNN (ms): Standard deviation of the RRI series, a representative variable in time-domain analysis influenced by both sympathetic and parasympathetic activity3. SDNNI (ms): SDNN index, mean of the standard deviation of RRIs extracted from 1-minute segments of time series data4. RMSSD (ms): Root mean square of successive differences between RRIs, measuring vagal contribution to HRV without being affected by respiration5. pNN50 (%): Percentage of RRIs greater than 50ms out of the total number of RRIs, reflecting PNS activity6. HTI: HRV triangular index, a geometric measure calculating the total number of RR intervals divided by the height of the RR intervals histogram, reflecting arrhythmias jointly with RMSSD, and less affected by noise and artifacts

Frequency-domain HRV Indices

7. TP (ms²): Total power of the density spectral8. LF (ms²): Absolute power of the low frequency (0.04-0.15 Hz) band, primarily reflecting SNS activity9. HF (ms²): Absolute power of the high frequency (0.15-0.40 Hz) band, reflecting parasympathetic nervous activity and periodicity of respiration10. LF/HF: Ratio of LF power over HF power, an index of sympathovagal balance measuring the relative contributions of SNS to PNS activity11. LFn: Normalized LF power; LFn = LF/(LF+HF);12. HFn: Normalized HF power; HFn = HF/(LF+HF); LFn and HFn have been demonstrated to be less sensitive to the changes in total power

Nonlinear HRV Indices

Nonlinear indices of HRV in this study will be derived from Poincaré plot analysis, a geometrical and nonlinear technique of phase-space characterization. The Poincaré plot is a scatter plot graphed by plotting every RRI against the prior interval and we can analyze it by fitting an ellipse to the points. This method provides a visual summary of heart behavior patterns buried in a time series.

13. S (ms): Area of ellipse, representing total HRV14. SD1 (ms): Standard deviation of the distance of each point from the y = x, measuring short-term HRV and correlated with baroreflex sensitivity (BRS)15. SD2 (ms): Standard deviation of each point from the y = x + average R–R interval, measuring both short-term and long-term HRV

Analyses of ECG-derived HRV indices are exploratory, with the goal of examining their potential relationships with treatment response and cognitive side effects.

### Outcomes

#### Primary outcome

The primary outcome measure is the change in HDRS-24 total score from baseline to the 12-week follow-up, which is assessed after the completion of the 12-session acute treatment phase (conducted over 4 weeks) and a subsequent 12-week post-treatment observation period. A reduction of at least 50% in the HDRS-24 score indicated a response to treatment, while a reduction of at least 60% in the HDRS-24 score and a total score of 8 or less indicated remission. Change in HVLT-R total recall score from baseline to the 12-week follow-up (assessing verbal memory, a key cognitive domain sensitive to seizure therapy effects).

#### Secondary outcomes

The secondary outcomes include: changes in HAMA, SDS, SAS, and GAF scores over time; changes in the seven secondary cognitive variables (TMT-A, BACS SC, Category Fluency Test, CPT-IP, WMS-III SS, BVMT-R, NAB Mazes); and changes in rsEEG and ECG HRV variables.

Relapse is defined as an HDRS-24 total score of 16 or higher, with at least a 10-point increase from the lowest post-treatment score, sustained across two visits at least 1 week apart. If rescue treatment (e.g., maintenance ECT, adjusted pharmacotherapy) is administered before Week 12, outcomes will be recorded up to the point of intervention to assess time-to-relapse.

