### Inclusion criteria

Participants must meet the diagnostic criteria for MDD as outlined in the Diagnostic and Statistical Manual of Mental Disorders, Fifth Edition (DSM-5).Participants must have a baseline score of 18 or higher on the 24-item Hamilton Depression Rating Scale (HDRS-24) (28).All patients are MST/ECT naïve and are required to be considered suitable for a course of ECT by both their treating psychiatrist and the study psychiatrist.During the trial’s treatment period, participants must be using a single antidepressant medication at a stable dose.Participants must be between the ages of 18 and 65 years.Informed consent from both parents and legal guardians is required.

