MST will be conducted at 100 Hz and 100% output using a pulse width of 350 μs and a peak intensity of the magnetic field at 3.0 Tesla. The duration of magnetic stimulation will be titrated using a 10-second train duration, starting from 2 seconds and increasing by 4 seconds in subsequent sessions, up to a maximum of 10 seconds (i.e., 200–1,000 pulses per session). In cases of poor seizure quality (<15 s), the stimulation duration increment will be set to 6 seconds in the next session. If no seizures were elicited, an additional 10-second stimulation will be administered immediately. Subsequent MST treatments will be maintained at a 10-second duration for a total of 1000 pulses.

EEG recordings during MST and ECT will be obtained using the Thymatron IV device with left and right frontal leads.

Patients will undergo identical preparation procedures, including the placement of earplugs and skin preparation for ECT electrode placement, irrespective of treatment allocation. To maintain blinding, the auditory stimulus from a recorded MST session will be played during ECT administration to prevent treatment allocation disclosure to individuals in adjacent rooms.

Completers will be defined as patients who received at least 8 treatments or achieved remission before the eighth treatment. Relapse will be defined as an HDRS-24 total score of 16 or higher, with at least a 10-point increase in HDRS-24 score sustained across two visits at least 1 week apart, the emergence of psychotic or suicidal symptoms, or the need for readmission to inpatient care.

While 12 sessions are standard for acute-phase treatment, the potential need for more sessions in MST will be explored through *post-hoc* analyses. This trial’s design prioritizes comparability with ECT’s typical acute regimen while allowing for long-term outcome assessment to capture delayed benefits.

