## Data entry and analyses

This trial aims to provide replicated evidence that MST is as effective as ECT in terms of remission rates, response rates, and reduction of depressive symptoms (assessed by the primary outcome: change in HDRS-24 from baseline to 12-week follow-up after the acute treatment phase) and superior in preserving verbal memory (via HVLT-R as an additional primary outcome), with fewer physical and cognitive side effects overall. Additionally, this study will explore personalized electrophysiological indicators (EEG/ECG) in an exploratory manner to inform future individualized treatment decisions for ECT and MST, and to generate hypotheses about the physiological mechanisms underlying the antidepressant efficacy and cognitive effects of MST/ECT. To our knowledge, this will be the largest RCT comparing ECT and MST in China. The trial will provide evidence to determine whether individualized treatment decisions based on personalized electrophysiological characteristics hold promise for optimizing the balance between efficacy and side effects (40). Specifically, it will offer insights into the potential effect sizes, acceptability, feasibility, and safety of the novel interventions under investigation. Predicting efficacy and side effects based on physiological characteristics, such as indicating greater side effects with ECT and comparable efficacy but fewer side effects with MST for patients with MDD, suggests that MST may be more suitable for these patients. Alternatively, physiological characteristics indicating superior efficacy with ECT compared to MST, with comparable side effects between the two, suggest that ECT may be more appropriate for these patients.

Firstly, data entry will undergo a thorough double-check to ensure accuracy. Data quality will then be assessed, with particular attention given to data distribution, and outliers will be excluded from subsequent analysis. Once data integrity is confirmed, detailed analyses of primary and secondary outcomes will be conducted using IBM SPSS Statistics 20 for Windows (Armonk, NY: IBM Corp).

Descriptive statistics, such as mean and standard deviation, will be computed for each study arm separately. Analyses will be performed within the intention-to-treat (ITT) framework to assess the effectiveness of interventions for all participants, utilizing multiple imputed datasets to address missing data.

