Appropriate statistical methods will be employed for data analysis, including mixed-effects models for repeated measures (MMRM). MMRM with a factorial design (3 time points × 2 conditions) will be conducted to examine significant interactions between time (baseline, Day 30, and Week 12) and condition (ECT and MST), while adjusting for potential covariates such as age, sex, duration of illness, age of onset, IQ, and antidepressant usage. This approach is robust to missing data under the missing-at-random (MAR) assumption and provides unbiased estimates of treatment effects. The significance level will be set at 0.05.

Sensitivity analyses will be performed to assess the robustness of results to missing data, including multiple imputation (MI) under MAR and missing-not-at-random (MNAR) assumptions. Results from MMRM and MI will be compared. Exploratory analyses will include subgroup analyses by demographic/clinical characteristics and correlation analyses between neurophysiological biomarkers (EEG/ECG) and treatment outcomes, using linear or logistic regression models as appropriate.

Subgroup analyses will compare relapse rates and time-to-relapse between participants who received maintenance treatments versus those who did not, within both MST and ECT groups. This will help disentangle the effects of acute treatment from post-treatment management strategies.

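### Neither relapse definition requires prior response, so relapse rate and time-to-relapse mix initial response with durability, and the planned maintenance comparison is distorted wherever response differs by maintenance status

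*Protocol article*

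**What the plan says.** The section on secondary outcomes states: "Relapse is defined as an HDRS-24 total score of 16 or higher, with at least a 10-point increase from the lowest post-treatment score". The rise must hold over two visits at least a week apart. The next sentence says that when rescue treatment is given before Week 12, outcomes are recorded only up to that point, to assess time-to-relapse.

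The section on ECT and MST procedures defines relapse again. It keeps the 16-point threshold and the 10-point rise, does not say what the rise is measured from, and adds "the emergence of psychotic or suicidal symptoms, or the need for readmission to inpatient care".

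The primary outcome section defines both states that could serve as a precondition: "A reduction of at least 50% in the HDRS-24 score indicated a response to treatment", and "a reduction of at least 60% in the HDRS-24 score and a total score of 8 or less indicated remission". Neither relapse wording refers to them. The inclusion criteria set an entry floor of 18 on the HDRS-24.

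The use of relapse is stated under Data entry and analyses: "Subgroup analyses will compare relapse rates and time-to-relapse between participants who received maintenance treatments versus those who did not, within both MST and ECT groups". The stated purpose is to separate the effect of acute treatment from later management. The only population statement is general: "Analyses will be performed within the intention-to-treat (ITT) framework to assess the effectiveness of interventions for all participants".

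**The concern.** Relapse is meant to describe loss of a benefit. As worded, the score rule applies equally to patients who had no benefit to lose. Everyone enters at 18 or more, so an unimproved patient is already past the 16-point threshold and only the 10-point rise decides. A patient who stays ill at a steady level never meets the score rule. The other wording lets such a patient qualify through symptoms or readmission.

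A relapse rate over all participants is therefore a weighted average of two different quantities: loss of response in responders, and further worsening or a clinical event in non-responders. Two groups with identical durability will show different relapse rates if their response rates differ. The planned contrast is between patients who did and did not receive maintenance treatment. Maintenance is not randomised, and response may well differ between those groups. The contrast could then show a maintenance effect that is only case mix, which defeats its stated purpose.

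**Working it through.** The article states no relapse figure, so there is none to reproduce. The response rates it cites from an earlier trial in the sample size section do reproduce: 18/35 = 51.4% (MST) and 16/38 = 42.1% (ECT).

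**1. The score rule for one patient.** Take entry at 26 and end of treatment at 22. Response needs 26 × 0.5 = 13 or less, so this is a non-responder. If 22 is the lowest post-treatment score, relapse needs 22 + 10 = 32, sustained. At a steady 22 the patient is above 16 throughout and never relapses.

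**2. What an all-participant rate measures.** Let p be the response rate, r the relapse rate in responders and q the rate at which non-responders meet the definition. The overall rate is p·r + (1 − p)·q. For two groups with the same r and q, the gap is (p₁ − p₂)(r − q). It is pure artefact, because durability is equal by construction. The values of r and q are assumptions; the article gives neither.

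**3. Size at the cited response rates.** Here p₁ − p₂ = 0.514 − 0.421 = 0.093.

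With q = 0, the gap is 10.3% − 8.4% = 1.9 points at r = 20%, 3.7 points at r = 40% (20.6% against 16.8%, before rounding) and 4.7 points at r = 50%.

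With r = 30% and q varied:

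| q | 51.4% response | 42.1% response | Gap (points) |
|---|---|---|---|
| 0 | 15.4% | 12.6% | +2.8 |
| 10% | 20.3% | 18.4% | +1.9 |
| 30% | 30.0% | 30.0% | 0 |
| 40% | 34.9% | 35.8% | −0.9 |

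**4. Is q below r under the score rule?** The score rule alone was simulated with assumed trajectories: mean baseline 28, visit-to-visit SD 5, responders worsening 2 points per visit. If non-responders do not drift, 6.3% of them relapse against 16.1% of responders, and the overall rates are 11.4% and 10.4% at the two response rates. If non-responders worsen at the same pace as responders, 17.9% of them relapse against 16.0%, and the overall rates are 16.9% and 17.1%. So q < r is plausible under the score rule but not assured. The additional routes in the other wording can only raise q relative to the score rule alone, and may raise r as well.

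**5. The comparison that is planned.** Suppose, purely as illustration, that 70% of maintained and 30% of unmaintained patients are responders, r = 30%, and maintenance has no effect.

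- q = 0: 0.70 × 30% = 21% against 0.30 × 30% = 9%.
- q = 10%: 21% + 0.30 × 10% = 24% against 9% + 0.70 × 10% = 16%.
- q = 30%: 30% in both.
- q = 40%: 21% + 0.30 × 40% = 33% against 9% + 0.70 × 40% = 37%.

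Maintenance would look harmful, neutral or helpful depending on q alone.

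**6. After restriction to responders.** Both groups show r, whatever their response rates, for example 30% against 30%.

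**The case against.** A reader might infer that the less effective arm will show the lower relapse rate, so that a weaker treatment is reported as more durable. The documents do not support this. No MST-versus-ECT relapse comparison is planned. Relapse is defined under the secondary outcomes heading but is not in the list of secondary outcomes. The direction also holds only while non-responders qualify less often than responders.

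A reader might also infer that non-responders are locked in as relapse-free for 12 weeks. That is wrong on three counts. They can worsen by 10 points. They can meet the symptom or readmission routes. Some have room to lose ground: a fall from 26 to 14 is 12/26 = 46%, a non-response, yet a later sustained 24 is a relapse. In addition, recording stops at rescue treatment, so a patient who stays ill and has treatment changed is not carried forward as a 12-week success.

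Two further objections have weight. The all-participant denominator is inferred from a general intention-to-treat sentence, and a full protocol or analysis plan may set the at-risk group. The artefact is also modest beside sampling error: at r = 40% and q = 0, the gap of 3.7 points compares with a standard error of √(0.206 × 0.794/105 + 0.168 × 0.832/105) = 5.4 points. The primary HDRS-24 outcome already counts unimproved patients against their arm.

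These arguments limit the size and the direction. They do not repair the rule. The article writes out the definition twice and announces an analysis that uses it, so the wording itself, and not only an unstated detail, is at issue. Even where the artefact reverses, the rate still does not measure durability of response.

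**Conclusion.** The point holds in a limited form. Neither definition requires prior response or remission, and no at-risk set is stated, so under the intention-to-treat wording relapse rate and time-to-relapse confound initial response with its durability. The comparison affected is maintenance versus no maintenance within each arm, and only where response differs by maintenance status. An MST-versus-ECT relapse statement would suffer in the same way if one were made.

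For a response difference as large as the one cited, the artefact is about 2 to 5 points when no non-responder qualifies and responders relapse at 20% to 50%. It falls to zero when non-responders qualify as often as responders and changes sign beyond that. Within an arm it could be larger, because nothing limits how far response differs by maintenance status. All values of r and q, the trajectories and the 70%/30% split are assumptions. The primary outcomes are not affected. The change should still be made, because the stated analysis cannot serve its purpose under this rule.

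**What to change.** 1. Reconcile the two relapse wordings, including the reference point for the 10-point rise and whether the symptom and readmission routes count.
2. Restrict relapse and time-to-relapse, including the maintenance comparison, to patients who met the article's response criterion at the end-of-treatment visit. Set time zero at that visit. Label the result descriptive, because the subset is formed after randomisation.
3. If a between-arm durability statement is to be made, base it on all randomised patients: response at end of treatment and no relapse through Week 12, with non-responders counted as failures.

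This costs a sentence or two in the outcome definition and a derived variable from data already collected. The downside is a smaller denominator for time-to-relapse: at 105 per arm and the cited response rates, 105 × 18/35 = 54 and 105 × 16/38 ≈ 44 patients, before any split by maintenance.

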### Study summary

**Figure 1** provides an overview of the study flow. Participants will be randomly allocated to either the ECT or MST group. Each center aims to recruit 15 participants for each group (ECT and MST), using block randomization, resulting in a total of 30 participants per center (15 per group). Across seven centers, this will yield a total sample size of 210 participants (105 per group). The trial comprises a 12-session intervention phase of ECT/MST, spanning approximately 4 weeks, followed by a 12-week observation period. For the first three treatment sessions, participants will receive consecutive sessions. Subsequently, there will be a one-day interval between sessions 4 to 6, a two-day interval between sessions 7 to 9, and a three-day interval between sessions 10 to 12, ensuring completion within a month. Following treatment completion, participants will undergo follow-up clinical observations every four weeks for 12 weeks. EEG and ECG recordings will be obtained at baseline, post-session 3, 6, 9, 12 (3 hours after each session), and at the 12-week follow-up. All evaluations will be conducted under standardized conditions throughout the sessions. **Table 1** delineates the time points for clinical assessments, interventions, and electrophysiological examinations.

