### Assessments

#### Clinical measures

Clinical assessments will be administered by blinded raters at various time points throughout the study, including baseline, post-session 3, 6, 9, and 12 (3 hours after each session), as well as at the 4-week, 8-week, and 12-week follow-up visits. The primary outcome measure was the total score on the 24-item Hamilton Depression Rating Scale (HDRS-24) (28). Additionally, the Hamilton Anxiety Scale (HAMA) (30), clinician-rated, served as a secondary outcome measure. Other assessments included self-reported measures such as the Self-Rating Depression Scale (SDS) (31) and the Self-Rating Anxiety Scale (SAS) (32), as well as clinician-rated measures including the Global Assessment of Functioning (GAF) scale (33). Follow-up assessments were conducted monthly. Prior to the commencement of the experiment, all subjects will undergo an interview using the MINI-International Neuropsychiatric Interview (M.I.N.I. 5.0) (34). Additionally, participants filled out a self-administered questionnaire to provide demographic information.

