### Additional treatments

As the primary objective of this trial is to evaluate efficacy, participants are restricted from receiving concurrent treatments for their depressive symptoms, except for one type of antidepressant medication, during the 30-day intervention period. However, the use of psychoactive medications and psychotherapy is allowed during the 12-week follow-up period, with detailed documentation of the type, dosage, and frequency/session of medication or psychotherapy.

During the 12-week follow-up period, participants may receive maintenance ECT, pharmacotherapy (e.g., antidepressants, mood stabilizers), or psychotherapy to prevent relapse. The type, dosage, and frequency of maintenance treatments will be recorded in detail to assess their impact on outcomes.

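### Relapse has two incompatible definitions, a score rise first seen at Week 12 can never be confirmed, and the same follow-up treatments are given conflicting roles in the relapse analysis

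*Protocol article*

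**What the plan says.** **Definition in Secondary outcomes.** Relapse is an HDRS-24 total of at least 16 "with at least a 10-point increase from the lowest post-treatment score, sustained across two visits at least 1 week apart". No other route is given.

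**Definition in ECT and MST procedures.** The threshold is the same, "with at least a 10-point increase in HDRS-24 score sustained across two visits at least 1 week apart", but the score from which the rise is measured is not named. Two clinical routes are added: "the emergence of psychotic or suicidal symptoms, or the need for readmission to inpatient care".

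**Visits.** Study summary says that, after treatment, "participants will undergo follow-up clinical observations every four weeks for 12 weeks". Clinical measures lists ratings after sessions 3, 6, 9 and 12, "as well as at the 4-week, 8-week, and 12-week follow-up visits". Table 1 agrees and places the session-12 rating on Day 30. No confirmation visit is described.

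**Treatment during follow-up.** Secondary outcomes gives maintenance ECT and changed drug treatment as examples of rescue. If rescue is given before Week 12, the rule is that "outcomes will be recorded up to the point of intervention to assess time-to-relapse". Additional treatments states that, in the same 12 weeks, "participants may receive maintenance ECT, pharmacotherapy (e.g., antidepressants, mood stabilizers), or psychotherapy to prevent relapse". Data entry and analyses then compares relapse rates and time-to-relapse, within each arm, between participants with and without maintenance treatment.

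**The concern.** Three things do not fit together.

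- **Who counts.** The two definitions classify some patients differently, and the article does not say which takes precedence.
- **Whether the score rule can be met.** A two-visit rule needs a second visit, and the last scheduled visit has none after it. If recording for time-to-relapse ends at rescue, a patient who deteriorates and is treated before the next visit may lack the second qualifying score as well. Both losses lower the count of score-based relapses.
- **What treatment means.** Maintenance ECT is an example of rescue that ends recording, a permitted means of preventing relapse, and part of what defines a relapse comparison group. Drug treatment has the same overlap. If recording ends when maintenance ECT starts, later relapse in that patient is not captured, and the maintained group can look relapse-free by construction.

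At stake are the relapse rate, the time-to-relapse analysis and the planned comparison by maintenance treatment.

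**Working it through.** The article gives no relapse rate, event count or power for relapse, so there is no figure of the plan's own to reproduce.

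**1. The definitions side by side**

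| | Secondary outcomes | ECT and MST procedures |
|---|---|---|
| HDRS-24 threshold | at least 16 | at least 16 |
| Rise of at least 10 points from | lowest post-treatment score | not stated |
| Two visits for the score route | yes | yes |
| Psychotic or suicidal symptoms | not a route | route |
| Need for readmission | not a route | route |

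A patient readmitted without two qualifying scores relapses under the second definition and not under the first. On the natural reading, the clinical routes need no second visit.

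**2. Which elevations can be confirmed**

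- First seen at Week 4: confirmable at Week 8.
- First seen at Week 8: confirmable at Week 12.
- First seen at Week 12: no later visit, so never confirmable.

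**3. Size of the loss.** Let w4, w8 and w12 be the shares of score-based relapses first seen at each visit, and r the probability of rescue between the first elevated visit and the next. Assume that elevations otherwise persist to the next visit and that rescue prevents confirmation. Then

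unconfirmable share = w12 + (w4 + w8) × r.

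The onset shares and r are assumptions; the article gives neither. Under a constant hazard with 12-week incidence p, h = −ln(1 − p)/12 and w12 = (e^(−8h) − e^(−12h))/(1 − e^(−12h)). For p = 0.20, e^(−12h) = 0.80 and e^(−8h) = 0.80^(2/3) = 0.862, so w12 = 0.062/0.20 = 0.31.

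| Assumed onset | w4 / w8 / w12 (%) | r = 0 | r = 0.25 | r = 0.50 | r at which half are lost |
|---|---|---|---|---|---|
| Even | 33 / 33 / 33 | 33% | 50% | 67% | 0.25 |
| Constant hazard, p = 0.20 | 36 / 33 / 31 | 31% | 48% | 65% | 0.28 |
| Constant hazard, p = 0.40 | 39 / 33 / 28 | 28% | 46% | 64% | 0.31 |
| Constant hazard, p = 0.60 | 44 / 32 / 24 | 24% | 43% | 62% | 0.34 |
| Early | 60 / 30 / 10 | 10% | 32.5% | 55% | 0.44 |
| Late | 20 / 30 / 50 | 50% | 62.5% | 75% | 0 |

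The r = 0 column follows from the visit schedule and the onset pattern alone. The other columns also need an assumed rescue rate.

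**4. In patients.** With 105 per arm and an assumed true score-relapse rate of 30%, there are 105 × 0.30 = 31.5 relapses. With even onset, the number counted is 31.5 × (2/3) × (1 − r): 21.0 at r = 0, 15.8 at r = 0.25 and 10.5 at r = 0.50.

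**The case against.** Several stronger readings are tempting, and the text does not support them.

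- **A reader might infer that four-weekly visits largely prevent confirmation.** They do not. A four-week gap satisfies a minimum of one week, and only Week 12 lacks a later visit.
- **A reader might infer that both definitions rest wholly on two visits.** In ECT and MST procedures that rule attaches to the score route. The clinical routes can capture some of the patients lost on score.
- **A reader might infer that no rise is possible at Week 4.** HDRS-24 is rated after session 12, on Day 30, and that rating can serve as the post-treatment reference.
- **A reader might infer that rescued patients are censored as non-relapsed.** The article does not say so. The recording rule is tied to time-to-relapse and does not clearly stop all ratings. Censoring rules are commonly left to an analysis plan.
- **A reader might infer that two thirds of relapses are missed.** That needs even onset and a 50% rescue rate, which appears nowhere in the article.

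It is also fair to say that relapse is defined under Secondary outcomes but is not in the list of secondary outcomes there, and that its only stated analysis is a subgroup comparison.

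All of this limits the size and reach of the point. It does not remove the conflict between the two definitions, the missing confirmation for Week 12, or the overlapping roles of the same treatments. These are stated in the article, so they are not details left to an unseen document.

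**Conclusion.** The point holds in this limited form. The two definitions are incompatible and must be reconciled. On the printed schedule the score rule cannot be met by an elevation first seen at Week 12, so score-based relapses are undercounted: by one third with even onset, by 24–31% under a constant hazard at an assumed 20–60% incidence, and by 10–50% across the other assumed onset patterns. Rescue before the next visit may add to this. Unless onset is late, more than half would be lost only if r exceeded about 0.25–0.44, and the article gives no rate against which to judge that. The sections that treat maintenance ECT and drug treatment as rescue, as prevention and as a comparison group also need reconciling. The effect is on the supportive relapse analyses. The primary HDRS-24 comparison and the sample size do not depend on it.

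**What to change.** 1. Give one relapse definition in both sections and state the reference score for the 10-point rise, for example the lowest score from Day 30 onward. Say whether the clinical routes count. Which definition to keep is for the investigators to decide.
2. Date the event at the first qualifying visit. Count a qualifying Week-12 score without a second visit, with a sensitivity analysis that excludes such events.
3. Keep recording HDRS-24 at the scheduled visits after rescue or maintenance treatment starts. Because treatment may lower the second score, also state how a qualifying score followed by treatment is counted.
4. Reconcile Secondary outcomes, Additional treatments, and Data entry and analyses, so that treatment started after a qualifying score is distinguished from preventive maintenance in the time-to-relapse analysis. Coding every start of rescue as a relapse is not a sound shortcut: the same treatments are permitted to prevent relapse, so well patients could be counted as relapsed and the comparison by maintenance treatment distorted.

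The cost is a wording amendment and one sensitivity analysis. The ratings fall at visits already scheduled. The downside is that an unconfirmed Week-12 event is slightly less specific. The changes should be settled before outcome data are seen by arm.
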